## **Outcome Measures**

We delay one week after treatment as the first evaluation timepoint (at 4 weeks) to exclude the local pain caused by treatment. Only affected knee will be evaluated from baseline throughout the entire study, if the unilateral osteoarthritis or the heavier knee in cases of bilateral osteoarthritis.

### **1. Primary Outcome Measure**

#### **Change in WOMAC [31]**

[ Time Frame: Change from baseline at 4 weeks]

Self-report measure of WOMAC total.

### **2. Secondary Outcome Measure**

#### **(1) Change in WOMAC**

[ Time Frame: Change from baseline at 16 weeks]

Self-report measure of pain, stiffness, and physical function subscale for KOA.

#### **(2) Change in Numeric Rating Scale of Knee Pain [32]**

[ Time Frame: Change from baseline at 4 weeks and 16 weeks]

Patients will rate their worst knee pain in the last 24 hours using an 11-point numeric pain rating scale with 0 representing “no pain” and 10 representing “ the worst pain imaginable”.

#### **(3) Change in Patient Global Assessment (PGA) [33]**

[ Time Frame: Change from baseline at 4 weeks and 16 weeks]

The PGA rating is a 11-point Numeric Rating Scale (NRS) in which patients will rate the degree to which their knee condition has changed from the time treatment was initiated to the present. The participant responds to the following query: “Please rate your overall knee’s condition from the time you began treatment until now.” using an 11-point NRS with 0 representing “A very great deal better” and 10 representing “A very great deal worse”.

#### **(4) OARSI Responder Criteria [34]**

[ Time Frame: At weeks 4 after randomisation]

Responder criteria included 1) greater than or equal to 50% improvement in WOMAC pain or WOMAC function and an absolute improvement of greater than or equal to 20, or 2) improvement in at least 2 of the following 3 scores: 20% improvement in pain and absolute change  $\geq 10$  on WOMAC pain score, 20% improvement in pain and absolute change  $\geq 10$  on WOMAC function score, or moderate or greater improvement ( $\leq 4$ ) on a 15 point global rating of change scale.

#### **(5) Number of Days With Restricted Activities About KOA**

[ Time Frame: Change from baseline at 4 weeks]

Restricted activity days, as an interim measure of disability assessment, will be evaluated through three questions regarding KOA. “bedridden at home for half a day or more”, “unable to go to work/school”, or “elimination of daily activities” due to KOA symptoms over the past week.

#### **(6) Change in 12-item Short Form Health Survey (SF-12) [35]**

[ Time Frame: Change from baseline at 4 weeks and 16 weeks]

The SF-12 is a generic health-related quality of life measure.

#### **(7) Change in the Mental Health Index (MHI-5) [36]**

[ Time Frame: Change from baseline at 4 weeks and 16 weeks]

Mental health will be measured by the Mental Health Index (MHI-5), which consists of a group of five items from the SF-36 survey. The MHI-5 evaluates patients’ overall mental health, encompassing depression, anxiety, emotional-behavioral regulation, and general positive mood, and in doing so, correlates strongly with the same composite measure used in the mental health scale.

**(8) Change in Perceived Stress Scale (PSS-10) [37]**

[ Time Frame: Change from baseline at 4 weeks and 16 weeks]

Psychological stress will be measured using the Chinese version of the Perceived Stress Scale (PSS-10). The PSS-10 is a widely utilized self-assessment tool that evaluates perception of stress over the course of approximately one month, and how daily routines, significant events, time assessment, and coping resources influence that experience. Therefore, the PSS is highly sensitive to changes in stress resulting from Tuina intervention.

**(9) Change in Tampa Scale for Kinesiophobia [38]**

[ Time Frame: Change from baseline at 4 weeks and 16 weeks]

The Tampa Scale for Kinesiophobia (TAMPA) is a 17-item scale that provides an important assessment of low back pain fear behaviors. A 4-point Likert scale, with a range from 1 to 4 (strongly disagree, disagree, agree, and strongly agree), was used. Higher scores indicate greater fear of movement. The TAMPA scale exhibits a high level of internal consistency, with a Cronbach alpha value of 0.78, and is also easily modifiable and responsive to variations in treatment.

**(10) Blinding Assessment**

[ Time Frame: At weeks 4 after randomisation]

To test whether the patients are blinded successfully, all patients will be asked to guess which kind of treatment they received.

**(11) Credibility/Expectancy Questionnaire [39]**

[ Time Frame: About 5 min after the first treatment]

The credibility and expectancy of patients will be measured using the Credibility/Expectancy Questionnaire.

**(12) Rescue Medicine**

[ Time Frame: At weeks 4 and 16 after randomization.]

Any use of pain-killers will be ascertained.

**3. Other Measures**

**Adverse events**

[ Time Frame: At weeks 4 after randomization.]

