## **Original Protocol (July, 2018 Versions)**

### **Objective**

A single-center parallel active-controlled, blinded randomized controlled trial design was used to verify the effectiveness and safety of Tuina therapy for knee osteoarthritis (KOA). The evidence has shown that manual Physical Therapy (mPT) is effective for KOA. Thus, we hypothesize that the effectiveness of Tuina is different from mPT for the patients with KOA in the changes of the Western Ontario and McMaster Universities Arthritis Index (WOMAC) after 8 treatments at week 4.

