## **Study Design**

### **1. Overview of Study Design**

This trial is a single-center parallel active-controlled, blinded randomized controlled trial that aims to compare the effectiveness of Tuina and mPT. A total of 140 qualified KOA patients will be randomly divided into either the Tuina group or mPT group at a ratio of 1: 1. In the Tuina group, patients will receive the Tuina therapy, and patients in the mPT group will receive joint mobilization, soft tissue manipulations, passive stretching, and strength training. They will both receive a total of 8 treatments in a 3-week course. Additionally, both groups will be provided health education and home-exercise instruction. Evaluations will be conducted at baseline (week 0) and 4 and 16 weeks. The primary outcome is the related symptoms of KOA, and secondary outcomes include health-related quality of life, treatment satisfaction, physical limitation, emotional and psychological stress, and adverse events. Figure 1 describes the flow chart of these procedures.

The study consists of 5 phases: recruitment, selection, baseline, treatment, and follow-up.

[figure not shown]

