**Figure 1 The flow chart**

**Recruitment:** Recruitment will be through multimodal strategies, (posters at the outpatient and community service centers, e-poster online, etc.);

**Selection (week -1):** Any patients who will be screened will be completing the case screening form. Those who met the screening criteria will be subsequently referred to a specialist for diagnosis and differential diagnosis. Ultimately, the eligible cases were enrolled in the study.

**Baseline (week 0):** Patients who satisfied the inclusion and exclusion criteria will be identified, randomly allocated, and completed the baseline evaluation period.

**Treatment (week 0-4):** Patients will be scheduled to be treated by practitioners for 8 sessions over 3 weeks, according to the randomization assignment;

**Follow-up (week 5-16):** Follow-up assessment will be operated by evaluators.

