**(11) Rescue medicine**

*[ Time Frame: At weeks 4, 8 and 16 after randomisation.]*

*Any use of pain-killers will be ascertained.*

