| SF-12                                    | X                                     | X                               | X                               | X                               |
| Blinding assessment                      |                                       | X                               |                                 |                                 |
| Credibility/Expectancy Questionnaire     | X                                     |                                 |                                 |                                 |
| Rescue medicine                          |                                       | X                               | X                               | X                               |
| Adverse events                           |                                       | X                               |                                 |                                 |

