## **Additional file 4-Statistical Analysis Plan**

### **1. Trial Design**

This is a single-center parallel active-controlled, blinded randomized controlled trial of comparing Chinese Tuina therapy and manual physical therapy (mPT) for patients with KOA. This trial aims to validate the effectiveness and safety of Tuina for KOA compared with mPT.

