### **2. Timing of outcome assessments**

Outcomes are collected at baseline, week 4, week 8 and week 16.

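### Safety versus mPT is a stated aim, but the current schedule asks about adverse events only at week 4, not at the week 8 and 16 visits, and the SAP plans no safety summary

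*Supplement*

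**What the plan says.** **The aim.** The protocol's Objective is to "verify the effectiveness and safety of Tuina therapy for knee osteoarthritis". SAP section 1 (Trial Design) makes this comparative: "This trial aims to validate the effectiveness and safety of Tuina for KOA compared with mPT". The protocol's Overview of Study Design ends its list of secondary outcomes with "emotional and psychological stress, and adverse events".

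**The schedule.** Under Outcome Measures, 3. Other Measures, the July 2018 text gives adverse events the time frame "At weeks 4 after randomization". The amended outcome list of May 2019 has no adverse-event entry of its own, so the current statement is Table 4. Its row "Adverse events" has one mark, in the week 4 column; weeks 8 and 16 are blank. SAP section 2 says: "Outcomes are collected at baseline, week 4, week 8 and week 16". The amendment sets rescue medicine to "At weeks 4, 8 and 16 after randomisation".

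**Treatment length.** The text with Figure 1 states: "Patients will be scheduled to be treated by practitioners for 8 sessions over 3 weeks".

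**The analysis.** SAP section 7 lists pain, function, overall assessment, responder rate and blinding. Section 8 gives methods for these. Neither mentions adverse events.

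**The concern.** The May 2019 amendment added a week 8 visit because the interval between weeks 4 and 16 was thought too long, and extended several items to it, including rescue medicine. The adverse-event row was not extended, and week 16 also stayed blank. A team that follows Table 4 sees every remaining patient twice more without a scheduled adverse-event question. The SAP then does not say how the events that are collected will be counted or compared.

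At stake is the reach of any safety statement. The plan expects some treatment-related discomfort: the section on possible risks anticipates local muscle and soft tissue pain, and the first outcome assessment is placed a week after treatment so that such pain does not affect it. Whether non-serious problems last, or begin after the course ends, is a natural part of a safety aim in a trial that follows patients to week 16. Without a defined summary, the choice of events, denominator and comparison would be made after the data are seen.

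**Working it through.** **1. Items at the post-baseline visits (Table 4).**

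| Item | Week 4 | Week 8 | Week 16 |
|---|---|---|---|
| WOMAC, NRS, PGA, SF-12 | yes | yes | yes |
| Rescue medicine | yes | yes | yes |
| Adverse events | yes | no | no |

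Two of the three post-baseline visits have no adverse-event item.

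**2. Time after the last scheduled question.** Follow-up ends at week 16 and the last adverse-event assessment is at week 4: (16 − 4)/16 = 12/16 = 75% of the weeks. Table 4 allows one week either side of the visit:
- Week 4 visit held at week 5: (16 − 5)/16 = 11/16 = 69%.
- Week 4 visit held at week 3: (16 − 3)/16 = 13/16 = 81%.

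**3. Exposure covered.** Treatment lasts 3 weeks. A visit at week 4 covers the whole course and about 1 week after it (4 − 3). At the limits of the window it covers 0 weeks (3 − 3) to 2 weeks (5 − 3) after the course. The gap therefore lies almost wholly after treatment, in about weeks 5 to 16.

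**4. Other provisions for events.**
- Possible risks and management: occurrences in the course of treatment, and how they were handled, are to be recorded. This is limited to the treatment period.
- Discontinuation and Dropout Criteria: a serious or harmful event at any time in the study can lead to suspension or discontinuation, and the cause of discontinuation is recorded. This is a rule for responding to an event that has become known. It does not schedule a question.
- Data Storage: serious-event reports are archived.

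None of these provides for asking all patients about non-serious events after week 4.

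**5. SAP sections 1 to 11.** Section 1 states the safety aim. Section 5 defines the intention-to-treat population for the primary analysis. Sections 7 and 8 have no safety outcome, count, proportion or comparison, and the sections on sensitivity analyses and missing data add none.

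**6. Denominators.** The note to Additional file 5 reports that 7 Tuina and 6 mPT patients did not provide the week 4 primary outcome, leaving 63 and 64 of 70. Assume that the same patients were not asked about adverse events; the documents do not say so. Dividing events by 70 would then multiply the proportion among assessed patients by 63/70 = 0.90 in the Tuina arm and 64/70 = 0.91 in the mPT arm, because unassessed patients would count as event-free.

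**7. Sample size.** The plan's one computed design figure is unaffected. A two-sample t calculation with difference 7, SD 13, two-sided α = 0.05 and 80% power gives 55.1, rounded up to 56 per arm. Then 56/0.8 = 70 per arm, or 140 in total, as stated. It is based on WOMAC and not on safety.

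**The case against.** The best defence is that adverse-event collection is placed where the exposure is. Treatment lasts 3 weeks, the week 4 visit looks back over all of it, events in the course of treatment are to be recorded anyway, and the one treatment risk the plan names is local pain after sessions. The efficacy hypothesis is also set at week 4, and neither statement of the safety aim mentions week 16. For a short manual therapy this is a defensible emphasis.

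Much of that stands, and it rules out stronger readings that a reader might infer:
- That the safety conclusion depends on a single recall at week 4. The instruction to record events during treatment contradicts this.
- That events after week 4 can never come to light. The discontinuation rule applies throughout the study and serious-event reports are kept, so serious events could surface.
- That later flares of knee pain would go unseen. NRS, WOMAC, PGA and rescue medicine are collected at weeks 8 and 16, and other treatments for the knee must be entered in the case report form. A flare present at a visit would show there, though it would not be recorded as an adverse event.
- That harms from home exercise would be missed. The plan does not say how long the exercises continue, and both arms receive the same instruction.
- That 75% of the safety information is lost. The figure weights all weeks equally, and the weeks of highest expected risk are covered.

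What the defence does not answer is why patients seen at weeks 8 and 16 are asked about rescue medicine but not adverse events, or how a comparative safety aim is to be met with no planned comparison.

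**Conclusion.** The point holds in a limited form. The treatment course is covered. Non-serious events that are delayed or persist, in about weeks 5 to 16, have no scheduled ascertainment, and two of the three post-baseline visits lack the item. By calendar time this is 12 of 16 weeks (69% to 81% with the visit window), a measure of schedule and not of risk. The missing SAP summary reaches further, since it also affects events during treatment; taken alone it is mostly missing detail.

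This does not make the safety aim unanswerable. As planned, the trial can describe safety to about week 4, with incomplete information after that. The primary efficacy analysis and the sample size are untouched. The conclusion assumes that Table 4 governs collection and that no separate safety procedure exists outside the documents shown.

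**What to change.** **Schedule.** In Table 4, mark adverse events at weeks 8 and 16 as well as week 4, and add a matching entry to the amended outcome list. Ask the same standard question in both arms at these existing visits.

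**SAP sections 7 and 8.** Add as safety outcomes the number and proportion of patients in each arm with at least one adverse event, at least one treatment-related event and at least one serious event. Give exact 95% confidence intervals for each proportion and the risk difference between arms. Report the number of patients assessed at each visit, so that those not assessed are not counted as event-free.

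**Cost.** Slightly longer visits at weeks 8 and 16 and one more table. No new visits and no change in sample size.

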**Table 2. Information collection content and time frame**

| Measures /Event                                  | Selection/baseline-1 st | Week 4-2 nd          | Week 16-3 rd         |
|--------------------------------------------------|------------------------------------|---------------------------------|---------------------------------|
| Collection time range                     | Week -1 or Week 0                  | Within one week before or after | Within one week before or after |
| Informed Consent Form                     | X                                  |                                 |                                 |
| Basic Information                         | X                                  |                                 |                                 |
| WOMAC                                     | X                                  | X                               | X                               |
| NRS                                       | X                                  | X                               | X                               |
| PGA                                       |                                    | X                               | X                               |
| OARSI Responder Criteria                  |                                    | X                               |                                 |
| Number of days with restricted activities | X                                  | X                               |                                 |
| SF-12                                     | X                                  | X                               | X                               |
| MHI-5                                     | X                                  | X                               | X                               |
| PSS-10                                    | X                                  | X                               | X                               |
| TAMPA                                     | X                                  | X                               | X                               |
| Blinding assessment                       |                                    | X                               |                                 |
| Credibility/Expectancy Questionnaire      | X                                  |                                 |                                 |
| Rescue medicine                           |                                    | X                               | X                               |
| Adverse events                            |                                    | X                               |                                 |

## Data Management Plan

### (1) Data Collection

Besides patient specific demographic and personal data (e.g., age, height) medical pre-conditions, previous treatment and previous medication will be documented. Beyond this, during the study, any clinical and treatment related data will be collected (see Table 2. Information collection content and time frame). All data will be retrieved from the CRF.

Information on all cases should be carefully and completely recorded on the CRF, whether the cases are in compliance with the trial protocol or are dislodged cases. The principal investigator shall be responsible for the authenticity of the trial data in the center. CRF annotation and writing of CRFs according to Clinical Data Interchange Standards Consortium (CDISC)'s Study Data Tabulation Model (SDTM) principles.

The data will be meticulously entered by two data entry clerks, ensuring accuracy through a double-entry method. The data entry clerks will be specifically trained with a comprehensive guideline tailored to the study's content. And the data entry process will accordance with the entry guidelines and the specified protocol.

### (2) Data Storage

The CRF form and all related original data will be submitted to the hospital where the research group is located for archiving. All cases, whether observed or discharged, should be completed by the requirements of the CRF.

**Information Kept by the Study Patients** Trial protocol, informed consent form, original reports of serious adverse events, etc.

**Information Kept by the Responsible Unit** Clinical trial application, preclinical trial information, Ethical materials, randomization schedule, surveillance report, CRF (completed, signed, and dated), serious adverse reaction report, etc.

### (3) Data Entry

As described above data will be taken directly from the CRF. Data will be entered to an electronic chart (Microsoft Excel 2010, Microsoft Corp., Redmond, WA, USA) by data entry clerks. All entered data will be cross-checked after entry for correctness. The data will be pseudonymized, processed and stored on PCs and servers of the Dongzhimen Hospital Affiliated to Beijing University of Chinese Medicine. These servers are expertly protected against access over several levels. Access is granted by a person responsible for IT at the hospital, and instructions are issued by the project management.

## Quality Control

**Rigorous Restriction of Enrollment** To control bias, one of the crucial methods utilized involves the rigorous implementation of inclusion criteria. This requires the setting of clear and comprehensive inclusion and exclusion criteria, which restricting the range of eligible patients, minimizing variation among patients, and ultimately supporting the formulation of objective conclusions regarding observed factors.

**Protocol Registered and Amend** Avoiding selective reporting bias in the publication phase of papers. Register the study protocol online prior to the start of the trial and make changes to the registration site timely in accordance with the progress of the study and changes to the study protocol

**Clinical Intervention** Before starting the trial, practitioners involved in the trial will be centrally trained with standarised operation procedures, and after training they will be assessed and qualified to participate in the study, and the implementation procedure will also be reviewed regularly.

**Evaluation Procedure** In order to ensure the consistency of evaluation, evaluator will receive a training to unify the procedure of evaluation. After training, strict assessment should be carried out to check the results of

training. And it is crucial that evaluator will not involve in participant screening, recruitment scheduling and treatment.

**The Content of Quality Control Personnel** One quality control personnel will be appointed to conduct quality checks through the study. The quality control personnel will conduct regular monitoring visits, plays a crucial role in overseeing the clinical trial.

- Assessing Protocol Adherence: The quality control personnel assesses whether the trial is being conducted according to the approved protocol. They review the procedures to ensure they align with the specified study design, interventions, assessments, and data collection. Any deviations or non-compliance are identified and addressed.

- Reviewing Data Accuracy and Completeness: Informed consent is crucial to ensure participants are fully aware of the trial's purpose, potential risks and benefits, and their rights. The quality control personnel will examine the informed consent process to confirm that participants have given their informed consent voluntarily. They review the consent forms, ensuring they are properly administered, signed, and dated. This helps ensure ethical and legal compliance. Additionally, the quality control personnel conduct thorough checks of the collected data to ensure accuracy and completeness. They review the entered conditions and compare it with the source documents. Discrepancies, errors, or missing information are identified and rectified to maintain data integrity.

**Improve the compliance of patients** Establishing a WeChat platform to ensure contact with patients, address issues related to KOA in their lives, and reduce discontinuation of cases.

